## Abstract

**Background:**

Hypertension is a serious global public health problem, and its incidence increases with age. Research has suggested that multiple antihypertensive prescriptions may be harmful to older individuals with hypertension. Baduanjin, a widely practiced physical activity in China, has been used as an adjuvant therapy to antihypertensive treatment in older individuals with hypertension. Therefore, the aim of the current study is to investigate whether Baduanjin exercise could reduce the need for antihypertensive medications in older patients.

**Methods:**

This single-center, open, randomized controlled trial will be conducted in China. Seventy eligible participants will be randomly assigned to either the 12-week Baduanjin exercise group or the 12-week aerobic exercise group (5 times a week), at a ratio of 1 : 1. The primary outcome will include the proportion of participants who reduce their antihypertensive medications. The secondary outcomes will include the changes in mean office systolic and diastolic pressure, 24-h ambulatory blood pressure, health-related quality of life (based on SF-36), and gut microbiota composition. *Discussion.* The results of this study will provide powerful evidence for the use of Baduanjin as an adjuvant therapy for antihypertensive medication reduction in older people with hypertension and therefore find the best treatment for hypertension. This trial is registered in the Chinese Clinical Trials Registry (ChiCTR1900024429).

## 1. Introduction

Hypertension (HTN) is an age-related chronic disease, and its incidence increases with age [1]. According to a survey from 2012 to 2015, the prevalence of HTN among elderly individuals aged ≥65 years is 55% in China [2]. Patients with HTN are at higher risks of cardiovascular diseases and stroke, with annual deaths reported to be up to 1 million [3]. HTN has significant social and economic costs, and its management is of high importance.

Angiotensin-converting enzyme inhibitors, angiotensin II receptor blockers, beta-blockers, calcium channel blockers, and diuretics are recommended for HTN by the European Society of Cardiology (ESC) and the European Society of Hypertension (ESH) [4]. In China, more than 35% of patients with HTN aged ≥65 years control their blood pressure (BP) by taking two or more antihypertensive medications as prescribed [5]. Research has suggested that multiple antihypertensive prescriptions may be harmful to older individuals [6, 7]. Indeed, it has been clinically reported that a considerable reduction in BP increases the risk of hypotension and syncope [8]. Furthermore, many patients with chronic conditions who are prescribed more antihypertensives have immense disease costs, which impacts their quality of life; consequently, nonadherence and nonpersistence are common [2, 9–14]. There is consistent evidence that patients under medication could benefit from regular physical exercise when adequately prescribed and consistently practiced. In this case, exercise can act as adjuvant therapy, exposing the patient to both medication and daily exercise [15].

Baduanjin is a mind-body integration of physical activity based on the traditional Chinese medicine theory, which cultivates qi to enhance the body's vitality. It is the most widely practiced form of traditional Chinese Qigong, dating back nearly 2500 years [16]. Baduanjin, also named eight-section brocades because it routinely consists of eight individual movements, is characterized by gentle postures, a meditative mind state, and breathing control, and each movement may also have salutary effects on different parts of the body or specific organs [17]. Recently, several studies have found that Baduanjin has beneficial effects on controlling BP in elderly patients who are intolerant to intense physical activities [18, 19]. Many clinical studies have described that Baduanjin exercise has beneficial effects on stabilizing glucose and lipids and improving quality of life [20–22]. Moreover, a previous randomized controlled trial has shown that short-term endurance exercise has effects on the gut microbiota diversity and composition in elderly individuals [23]. Given these findings, Baduanjin exercise may be suitable for older patients with limited daily activity and long-term antihypertensive treatment. Thus, Baduanjin is expected to become an adjuvant therapy for medication reduction in older patients with HTN.

No previous trial has evaluated the use of Baduanjin exercise-based training as an adjuvant therapy to reduce antihypertensive medications in older patients. Therefore, we designed a single-center, open, randomized controlled trial (RCT) to investigate the effect of Baduanjin exercise acting as adjuvant therapy on antihypertensive medication reduction in older patients with HTN and investigate the changes of office blood pressure, 24-h ambulatory blood pressure, health-related quality of life, and composition of gut microbiota.

## 2. Methods

### 2.1. Study Design

This study is a single-center, open, randomized controlled trial that will be conducted at the Guang'anmen Hospital of the Chinese Academy of Medical Sciences. The research period will cover June 2019 to June 2022. Seventy eligible patients will be randomly assigned to either the Baduanjin exercise or aerobic exercise groups for 12 weeks. The outcomes will be assessed at 12 weeks (immediately after the intervention). The study design process is shown in the study flow chart in Figure 1. The protocol of this clinical trial complies with Standard Protocol Items: Recommendations for Interventional Trials guidelines [24] and follows the Consolidated Standards of Reporting Trials [25].

### 2.2. Recruitment

We will adopt a series of recruitment strategies, including recruiting general outpatients and inpatients of the Guang'anmen Hospital of the China Academy of Chinese Medical Sciences Comprehensive Geriatric Department and posting posters in the hospital. The study investigators will communicate with potential patients and discuss the details of the study. The potential participants will be given information about the study, including the study purpose, process, intervention methods (Baduanjin exercise and aerobic exercise), and the possible side effects. A screening procedure will be performed, and those who are eligible and wish to participate will sign informed consent.

### 2.3. Screening Procedure and Eligibility Criteria

Following provision of informed consent, the demographic characteristics, history of disease, medication use (including the name, usage, dosage, and frequency of medications), and office BP will be collected to identify eligible patients. Patients will be eligible to participate in the study if they fit the eligibility criteria. The screening procedure will be completed before randomization.

#### 2.3.1. Inclusion Criteria

Male or female, between 65 and 80 years old.Office BP: 120 ≤ systolic pressure (SBP) < 140 mmHg, diastolic pressure <90 mmHg (according to the baseline measured office BP).Stable dose of antihypertensive drugs for at least 3 months.Treated with a moderate dose of two or more antihypertensive drugs for at least 12 months. According to the guidelines, antihypertensive drugs are defined as five major drugs: angiotensin-converting enzyme inhibitors, angiotensin II receptor blockers, beta-blockers, calcium channel blockers, and diuretics (thiazides and thiazide-like diuretics such as chlorthalidone and indapamide).Eligible patients must be willing to participate in the study and provide informed consent.

#### 2.3.2. Exclusion Criteria

Secondary HTN or previous accelerated or malignant HTN.Severe cardiovascular diseases, pulmonary diseases, liver diseases, kidney diseases, nervous diseases, psychiatric disorders, cancer, infectious diseases, or others, limiting the ability to participate in the Baduanjin or aerobic exercise programs and influencing the reduction of antihypertensive medications.Using other drugs that may affect BP.Smoking and/or alcohol abuse.Women who are pregnant or planning to become pregnant.Enrolled in other clinical trials in the last 3 months.Practiced Baduanjin or other similar physical activities in the past 3 months, such as Qigong, yoga, or Tai Chi.

### 2.4. Randomization

Each participant will be randomly assigned to either the Baduanjin exercise group or the aerobic exercise group at a ratio of 1 : 1. The allocation sequence will be generated by the SAS software v.9.4 PLAN program and managed by an independent statistician who will not anticipate in the recruitment, evaluation, and intervention of participants. The statistician will put the list in a sealed, opaque, sequentially numbered envelope and give it to the investigators after sealing. Participants will be recruited in a natural, unpredictable order. After screening, the investigator will open an envelope sequentially to obtain a random number and determine whether the participant will be exposed to Baduanjin exercise or not.

### 2.5. Blinding

Baduanjin exercise is a familiar exercise for the Chinese population, and blinding is impossible to achieve at the level of related investigators, exercise coaches, and participants. However, the outcomes will be independently assessed by two statisticians in a blinded manner.

### 2.6. Intervention

#### 2.6.1. Baduanjin Exercise Group

Participants randomized to the Baduanjin exercise group will collectively practice Baduanjin at the Guang'anmen Hospital of the China Academy of Chinese Medical Sciences. A professional coach at the Beijing University of Traditional Chinese Medicine will guide the training of participants and supervise them throughout the entire intervention period. Each session will last for 30 min (including 5 min of warm-up, 20 min of Baduanjin training, and 5 min of relaxation), 5 times a week, over the course of 12 weeks. The training program will be formulated following the Healthy Qigong Baduanjin published by the State Sports General Administration and will consist of 10 postures in total (Figure 2) (including the preparation pose and the ending pose). In the continuous training, the patient's heart rate (HR) will be monitored by a polar heart rate monitor, and the exercise intensity and energy expenditure will be constant at 55%–75% of the peak HR. All participants will be instructed to maintain their usual activities and refrain from new strength training.

#### 2.6.2. Control Group

Participants randomized to the aerobic exercise group will collectively practice moderate-intensity walking exercise at the Guang'anmen Hospital of the Chinese Academy of Chinese Medical Sciences, at a frequency of 5 times a week, over a 12-week period. A professional coach will be hired to guide the training and supervise the participants throughout the intervention. Each session will consist of a 5-min warm-up, 20-min walking training, and 5-min relaxation. In the continuous training, the patient's HR will be monitored by the polar heart rate monitor, and the exercise intensity and energy expenditure will be constant at 55%–75% of the peak HR. All participants will be instructed to maintain their usual activities and refrain from new strength training.

### 2.7. Outcome Measurements

Table 1 outlines the primary and secondary outcomes to be undertaken during the study. The primary outcome will be examined at postintervention (week 12). The secondary outcomes will include office BP, 24-h ambulatory blood pressure monitoring, health-related quality of life, and gut microbiota composition, all of which will be measured at baseline (week 0) and postintervention (week 12).

#### 2.7.1. Primary Outcome

The primary outcome will be the proportion of participants with antihypertensive medication reduction postintervention; this will be defined as a reduction of at least 15% of total antihypertensives compared with the baseline medical prescription after the 12-week exercise procedure (e.g., patients using 2 or 3 medications need to reduce ≥50% of 1 medication to achieve the primary outcome and patients using 4 or 5 medications need to reduce ≥1 medication). Guidelines recommend that in older patients (>65 years), treated SBP should not be targeted to <120 mmHg; when the SBP is <120 mmHg, the risk of harm appears to increase and outweigh the benefits [4]. Hence, once participants begin to practice Baduanjin or aerobic exercise, they will be required to return for a routine clinical examination every 4 weeks (including office BP measurement and maintenance of antihypertensive drugs); when office BP is <120 mmHg, we will reduce the number of medications taken by the patients.

Once a medication has been reduced, research assistants will closely monitor the participant's response to the reduction (through BP). The research assistants will perform the monitoring according to the procedures outlined in Figure 3, although these will be flexible. The participants will be required to return for at least one routine BP check (every 4 weeks); when the patients' BP is >150 mmHg or when adverse events (AEs) occur, the general practitioners (GPs) will be contacted, and the medication (dose or type) will be readjusted to ensure that the incidence of severe AEs occurring by medication will be very low.

*(1) Self-Monitoring*. Participants will optionally self-monitor their BP at home when they reduce their medication. The protocols developed in the Telemonitoring and Self-Management in Hypertension (TASMIN) trials [26, 27] have been modified and simplified to suit this study. These reduced medications will be monitored using revised protocols. Following training, participants will be advised to conduct self-monitoring at least four times during the BP check week (4 times weekly) after drug withdrawal.

If four or more BP readings recorded during the BP check week are higher than clinically safe (e.g., home SBP > 150 mmHg), the research assistants and GP will be contacted, and the medication will be changed according to the original plan. Previous meta-analyses have provided good evidence that self-monitoring differences will not impact the study results but only affect when combined with interventions [28].

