### 2.9. Data Collection and Management

After recruiting participants, investigators and a professional coach will guide the training of participants and supervise them throughout the entire intervention period. Especially, participants will be required to return for a routine clinical examination every 4 weeks and monitor the participant's response through WeChat until the end of the study. As for the participants who discontinue or deviate from intervention protocols, investigators will call and WeChat participants to minimize data loss and participant withdrawal or loss during the study period.

Every participant should follow the instruction during the study period, and their related information should be recorded and stored as a print-based case report form (p-CRF). The electrical CRF should be stored in an encrypted mobile hard disk along with the procedure of filling in the p-CRF. All basic information of participants will be protected by the researching group, and a unique identified number will be applied during the procedure of the study. The mobile hard disk, p-CRF, and informed consent will be stored in the office of the Guang'anmen Hospital of the China Academy of Chinese Medical Sciences.

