### 2.11. Statistical Analysis

This study will be based on intention to treat (ITT), and the results will be analyzed in accordance with the principle of ITT analysis. Statistical analysis will be performed at two prespecified time points and will be used to determine primary and secondary outcomes. Data from all patients who complete the follow-up will be analyzed according to the group in which they were originally defined. Participants who received reduced medication in the primary outcome analysis will be defined as those who received reduced medication during the exercise intervention and maintained it until the end of the study. The chi-square test or Fisher's exact test will be used to compare the proportion of patients with a primary outcome event between the two study groups. For the secondary outcomes, measurement data will be expressed as mean ± standard deviation (SD), and independence test, normality test, and homogeneity test of variance will be performed for each group. In addition, repeated measurements over time will be analyzed using analysis of variance (ANOVA of repeated measures), and pair comparisons between groups will be performed using the LSD *t*-test (homogeneity of variance) or Tamhane's T2 test (heterogeneity of variance). The composition of the gut microbiota will be analyzed using a nonparametric Mann–Whitney U test for relative bacterial abundance (at baseline and between groups). A Wilcoxon matched-pairs test will be used for comparison to analyze the differences in relative bacterial abundance between the Baduanjin and aerobic intervention groups. A *P*

-value of <0.05 will be taken to indicate a significant difference. All analyses will be performed using the SPSS v.17.0 software package. Every effort will be made to minimize data loss and participant withdrawal or loss during the study period; if the primary outcome or potential confounders' data are missing, a multiple imputation method will be used to fill in missing data.

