### 2.12. Safety Assessment

AEs may include medication withdrawal AEs (defined as the 10 most commonly reported AEs: stiff joints, pain, fatigue, loss of strength, breathlessness, sleep difficulties, pins and needles, sore eyes, dizziness, and impotence), exercise injury, and fall [27]. Serious AEs (SAEs) include, among others, prolonged hospital stay, disability, and death. AEs and SAEs will be recorded during the 12 weeks of intervention from enrollment. If either occurs during the study, the investigators will evaluate the relationship between the events and the intervention and report it to the Ethical Committee and DSMB; subsequently, they will decide whether the participant should withdraw from the trial.

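### A drug cut at the week-12 visit has its required BP check after safety recording ends, and the two statements of the primary outcome do not clearly agree on whether it counts

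*Protocol article*

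**What the plan says.** All references are to the protocol article.

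- **Visits and trigger.** Sections 2.7.1 and 2.9 set the same interval; in Section 2.9, "participants will be required to return for a routine clinical examination every 4 weeks". Section 2.7.1 gives the trigger: "when office BP is <120 mmHg, we will reduce the number of medications taken by the patients". No visit is exempted.
- **After a cut.** Section 2.7.1: "The participants will be required to return for at least one routine BP check (every 4 weeks". If BP exceeds 150 mmHg or an AE occurs, the general practitioner is contacted and the drug is readjusted. Home readings are optional. Monitoring follows Figure 3, which is not shown and which the text calls flexible.
- **When the outcome is read.** Section 2.1: "The outcomes will be assessed at 12 weeks (immediately after the intervention". Section 2.7: "The primary outcome will be examined at postintervention (week 12". Table 1 places an office BP at the end of the intervention.
- **Safety window.** Section 2.12: "AEs and SAEs will be recorded during the 12 weeks of intervention from enrollment".
- **Who is a responder.** Section 2.7.1 requires a reduction of at least 15%, "compared with the baseline medical prescription after the 12-week exercise procedure". Section 2.11 describes responders in the primary analysis as "those who received reduced medication during the exercise intervention and maintained it until the end of the study".

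**The concern.** Two things do not fit together when the cut is made at the last visit.

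The first is safety. The check that Section 2.7.1 requires after a cut exists to catch a rise in BP or a withdrawal AE. For a cut at week 12 it falls about four weeks after AE recording stops. Participants are 65 to 80 years old, and supervised exercise ends at the same moment as the drug is reduced. Withdrawal AEs are the first category that Section 2.12 lists, yet for these participants the stated window closes before such events could appear.

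The second is classification. The primary outcome is stated in two places, and a week-12 cut fits one statement and not clearly the other. The investigators who see participants at these visits know the allocation (Section 2.5), so the rule should be settled before data are seen.

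**Working it through.** No figure in the plan needs to be reproduced for the timing point. It follows from the calendar.

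**Step 1: timing.** Four-weekly visits over 12 weeks fall at weeks 4, 8 and 12 (inferred; the article does not list them). The first routine check after a cut at week *t* falls at *t* + 4.

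| Cut at week | Required check at week | By the week-12 outcome reading? | Within the 12-week AE window? |
|---|---|---|---|
| 4 | 8 | yes | yes |
| 8 | 12 | yes | yes |
| 12 | 16 | no | no |

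Section 2.9 continues visits and contact to the end of the study, but no section dates a participant's end later than week 12.

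**Step 2: the two outcome statements.** Take a participant whose first cut is at week 12 and is large enough.

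- Section 2.7.1 compares the prescription after the programme with baseline. It is lower, so the participant is a responder.
- Section 2.11 asks that the cut be made within the intervention and kept. A cut at an assessment held just after the intervention is either too late, or has been kept for no time at all. Neither shows maintenance.

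**Step 3: how many, as an illustration only.** The share of responses that first arise at week 12 is not in the article. I assume 10%, 20% and one third (the last if responses arise evenly over three visits), equal in both arms. Section 2.8 plans 40% against 10%, with 35 per arm. Expected responders: 35 × 0.40 + 35 × 0.10 = 14 + 3.5 = 17.5. Week-12 cuts among them: 17.5 × 0.10 = 1.75; 17.5 × 0.20 = 3.5; 17.5 × 1/3 = 5.8. That is about 2 to 6 of 70.

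**Step 4: power if these cuts are not counted.** This assumes that the planned 40% and 10% include them. For two proportions, two-sided 5%, *n* per arm, with p̄ the mean of the two:

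power = Φ{ [ |p1 − p2|√n − 1.96√(2p̄(1 − p̄)) ] / √(p1(1 − p1) + p2(1 − p2)) }

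With none removed and n = 35: (0.30 × 5.916 − 1.96 × 0.6124) / 0.5745 = 1.00, so power is 84%.

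| Share at week 12 | Rates left | Power, 35 per arm |
|---|---|---|
| 0 | 40% vs 10% | 84% |
| 10% | 36% vs 9% | 78% |
| 20% | 32% vs 8% | 72% |
| one third | 26.7% vs 6.7% | 62% |

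If the planned rates already leave out week-12 cuts, there is no loss against plan. (The stated 30 per arm for 90% power is not reproduced by the matching sample-size formula, which gives 42. That is a separate matter and does not affect this point.)

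**The case against.** The strongest reply has four parts.

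1. *Week 12 may not be a cutting visit, and Figure 3 may cover the period after it.* Both are possible. The figure's title refers to monitoring after exercise. This stands as a limit: the point rests on the literal text. It does not remove the conflict with the AE window in Section 2.12, which is stated without exception.

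2. *The post-cut check is a safety step, not a condition of response.* This is right. A reader might infer that every responder had to be checked on the reduced drug before being counted, and that week-12 responders are therefore invalid. Section 2.7.1 does not say so. Nor does the text leave these participants without care: it still obliges a return visit and contact with the general practitioner. What is missing is the recording.

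3. *Section 2.11 is the more specific rule and simply excludes week-12 cuts.* This is a fair reading. But Section 2.7.1 carries the formal definition and would include them, and the end of the study is not dated, so the two need aligning.

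4. *Handling of a last-visit event belongs in the analysis plan.* Often so. Here, however, the article itself states the outcome twice, in terms that can classify one participant differently.

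A reader might also infer a large loss of power. Simulations with assumed BP means, SDs, falls and rebound give losses from 0 to 29 points if week-12 cuts are dropped. None of those inputs is in the article, and the worked cases give walking-arm response rates of 26% to 40% against the planned 10%. They do not support a figure for this trial.

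**Conclusion.** The point holds in a limited form. Read literally, the article permits a cut at week 12, requires a BP check about four weeks later, and stops recording AEs before that check. It also leaves unsettled whether such a cut is a primary outcome event.

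The timing result rests on one inference, that visits fall at weeks 4, 8 and 12, and on Figure 3 not saying otherwise. The number of participants affected, and the loss of events and power if week-12 cuts are not counted, cannot be estimated from the article; Steps 3 and 4 illustrate them under assumed shares.

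It would go too far to say that the comparison is biased or the type I error inflated. The same rule applies in both arms, and the documents give no ground for either claim. Nor do they require that response be judged at week 16.

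**What to change.** **Safety.** In Section 2.12, record AEs until the post-cut BP check that Section 2.7.1 already requires, and name that check in Sections 2.1 and 2.7. Suggested text:

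*For a participant whose medication is first reduced at week 12, AEs and BP are recorded until the BP check four weeks later (week 16). This check takes place after supervised exercise has ended.*

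**Classification.** In Sections 2.7.1 and 2.11, put the same rule, chosen before data are seen:

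*A reduction first made at the week-12 visit [is / is not] a primary outcome event. The number of such reductions is reported by arm, and the primary analysis is repeated under the other rule.*

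Counting them keeps all three visits but includes responders with no time on the reduced drug. Not counting them respects the maintenance wording of Section 2.11 but lowers the event rate and power. A third choice, counting a week-12 cut only if it is still in place at week 16, is optional: it would judge some participants later than others and off the programme.

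**Cost.** A few sentences, one BP visit that is already required, and four more weeks of AE recording for a small number of participants. The trigger, the 120 and 150 mmHg thresholds, the test and the planned 70 participants stay as they are.
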